**Figure 2 F2:**
[figure not shown]
Combined physical activity score based on the activity quartiles of the PAM and AQUA.

### Intervention

The subjects classified as relatively inactive will be invited to take part in the intervention study. For the intervention study they will be required to fill in a questionnaire and to participate in physical measurements (i.e. baseline measurements). After completion of the baseline measurements the participant are randomly assigned to the intervention or the control group. Participants in the intervention group receive the PAM monitor and have access to their personal website (COACH) for a 3-month period. The participants are given written and verbal instructions and practical demonstrations on how to wear the PAM and how to use the COACH. Special attention is paid to:

1. placing the PAM on the hip;

2. connecting the docking station to the computer;

3. installing the software on the computer;

4. registering and logon to the PAM COACH website;

5. setting a PAM goal and reading the results at the COACH website.

The control group receives a single written information brochure with general recommendations and guidelines for physical activity. Telephone numbers and an e-mail-address are provided in case questions arise. At each intervention site at least one computer with PAM software is arranged.

### Measurements

The primary outcome of the intervention study is the level of physical activity measured by questionnaire. Secondary outcomes are determinants of PA, quality of life, empowerment, aerobic fitness and body composition. A compact questionnaire is constructed to maximize the response and minimize time spent filling in the questionnaire. All measurements are performed at baseline and after 3 months of intervention. Five months after the 3 months intervention only the questionnaire is repeated.

### Questionnaire

#### Physical activity

The Activity Questionnaire for Adolescents & Adults (AQUA) is a short questionnaire developed to assess physical activity and sedentary activity at work, at school, during leisure time and transportation. The structure of the AQUA is obtained from the SQUASH-questionnaire [20]. Information on light (range for adolescents, 2–5 MET and adults 2–4 MET), moderate (range for adolescents, 5–8 MET and adults 4–6.5 MET) and vigorous (adolescents, >8 MET and adults >6.5 MET) intensity physical activities are obtained, as well as information on sedentary behaviour (<2 MET), such as TV viewing and computer usage. The AQUA refers to activities in the past week (7-day recall). Physical activity will be expressed in minutes per week and in a total activity score. The total activity score will be calculated by multiplying the minutes per week by the actual MET score of the specific activity (MET/min/week).

#### Determinants of physical activity

In this questionnaire, the enquired determinants of physical activity refer to three categories of activity: sport, transportation and sedentary activities. To minimize time spent filling in the questionnaire for each determinant of physical activity a selection of two or three relevant questions is made. The following determinants of physical activity are assessed in both age groups:

***Behavioural intention ***is the cognitive representation of a person's readiness to perform physically active behaviour, and it is considered to be the immediate antecedent of behaviour. Behavioural intention was measured with one item (i.e. 'Do you intend to play sport more in the following three months?' with response categories ranging from 1 = 'no, certainly don't' to 5 = 'yes certainly do'). According to the Theory of Planned Behaviour [21], behaviour in general is determined primarily by behavioural intention and postulates that this intention is determined by three constructs: attitude, subjective norms and perceived behavioural control.

***Attitude***, the beliefs that are associated with physical activity behaviour and the evaluations of these beliefs. The questionnaire contains two questions about attitude (i.e. 'I like playing sports?' with response categories ranging from 1 = 'strongly disagree' to 5 = 'strongly agree').

***Social influences ***[22] such as social norms, social expectations, modelling and imitating. Social norms are determined by the normative beliefs of significant others about physical activity behaviour and the individual motivation to comply with these persons. The questionnaire of the young adults contains five questions about social influences [23], the questionnaire of the adolescents contains four questions regarding social influences (i.e. 'My friends think I should play sports' with response categories ranging from 1 = 'no, certainly don't' to 5 = 'yes certainly do'). For the categories sport and transportation, two questions about modelling are added.

***Self-efficacy expectations***, which are beliefs of a person about his abilities to perform physical activity. Increased self-efficacy will result in improved performance of this behaviour. The questionnaire contains two questions about self-efficacy [24] (i.e. 'Do you think you can manage to play sports for at least half an hour a day?' with response categories ranging from 1 = 'no, certainly don't' to 5 = 'yes certainly do').

***Knowledge of daily physical activity ***is asked by one item (i.e. 'How much physical activity do you have to spend per day to stay healthy'?) with the response categories: one hour per week, three hours per week, thirty minutes per day, one hour per day, two hours per day no and don't know).

For the categories sport and transportation two extra determinants are assessed:

***Personal barriers***, many personal variables, including physiological, behavioural, and psychological factors, may affect our plans to become more physically active. Three items about personal barriers are asked [24] (i.e. 'Do you think you can manage to play sports when it rains?' with response categories ranging from 1 = 'no, certainly don't' to 5 = 'yes certainly do').

***Awareness of physical activity***, one item is included in the questionnaire (i.e. 'Do you think you spend enough time playing sports?' with the response categories yes and no). Awareness of the actual level of activity will be assessed by comparing the outcomes of the awareness questions with the total minutes per week of the concerning activity (i.e. sport, walking/cycling) from the questionnaire.

#### Quality of life

The quality of life of the adolescents is assessed by the Dutch version of the KIDSCREEN-10 Index [25]. The KIDSCREEN is a health related quality of life-measure (HRQOL) and applicable for healthy children aged from 8 to 18 years. The KIDSCREEN measures 10 HRQOL dimensions (Physical-, Psychological Well-being, Moods and Emotions, Self-Perception, Autonomy, Parent Relations and Home Life, Peers and Social Support, School Environment, Bullying, Financial Resources) by 11 items on a five-point scale, ranging from 1 "completely not" to 5 "completely". From the total score t-values and percentages will be calculated by age and gender.

The quality of life of the young adults is assessed by the SF-36 Health Survey (SF-36) [26,27]. The SF-36 provides a health related quality of life measure and is applicable for adults. The SF-36 is composed of 36 questions and standardized response choices, organized into eight multi-item scales: physical functioning, role limitations due to physical health problems, bodily pain, general health perceptions, vitality, social functioning, role limitations due to emotional problems and general mental health. All raw scale scores will be linearly converted to a 0 to 100 scale, with higher scores indicating higher levels of functioning or well-being. Item score and subscale scores will be calculated.

#### Empowerment

In both age-groups, empowerment is assessed with a Dutch version of the Pearlin Mastery Scale [28]. This scale refers to the extent to which a person has the feeling of being in control of his or her own life. The questionnaire consists of seven statements, such as 'Some of my problems I can't seem to be able to solve at all', with response categories ranging from 1 = 'strongly disagree' to 7 = 'strongly agree'. Higher scores on the scale indicate a greater sense of mastery. A total score will be calculated.

#### Process evaluation

Among the participants of the intervention group experience with the use of the activity monitor and the personal COACH will be evaluated. This will be assessed with a brief questionnaire with both qualitative and quantitative questions about the usage of the PAM and the PAM COACH website and possible problems that may have been experienced. Reasons for complying or not complying will be collected also, in order to obtain insight into the potential success or failure of implementation and long-term adherence user implementation.

### Physical measures

#### Aerobic fitness

In adolescents, the aerobic fitness is assessed by the 20 meter shuttle-run test (20 mSRT) [31,32]. The 20 mSRT is a maximal aerobic running test. The test starts at a speed of 8.0 km/h, which increases each minute by 0.5 km/h. To perform the test, the subject runs a 20-meter course back and forth. The pace is set by an audio signal. The test has been shown to be reliable and valid field test to estimate maximal aerobic capacity [31,33]. Changes in 20 mSRT score will be used as a measure for changes in aerobic capacity. The 20 mSRT is chosen for adolescents because the test can easily be carried out during the PE classes and most of the students are acquainted with the test.

In young adults, the aerobic fitness is assessed by the Chester Step Test (CST). Previous to every test each employee is screened with the Physical Activity Readiness Questionnaire (PAR-Q [34]). The PAR-Q will be interpreted by qualified staff. The CST is a submaximal test to predict aerobic capacity. The CST consists of increasing paces of stepping on and off a bench (on, on, off, off). The height of the bench is determined based on the age and self reported physical activity in the past week of the employee. The CST commences at the relatively slow pace of 15 steps per minute and increases every two minutes to 20, 25, 30 and 35 steps per minute. The stepping beat is set by a metronome (Yamaha Corporation, QT 1B). Throughout the test the heart rate is monitored continuously with a Polar (S610i) heart rate monitor (Polar, Electro Oy, Kempele, Finland). After each stage the subject will be asked to rate his perceived exertion on the Borg scale [35] which is a 15-point numerical rating scale, ranging from 6 "very very light" to 20 "exhaustion". The test is terminated when the subjects' heart rate reaches 80 percent of the age predicted maximal heart rate (i.e. 220 minus age), or when the subject rates 14 on the Borg scale. Aerobic capacity is predicted by the provided Chester Step Test calculator (ASSIST creative resources Limited, Wrexham, England). Changes in the CST score will be used as a measure for changes in aerobic capacity [36,37]. The CST is chosen for employees because the test is easy to perform at the worksite and it takes little time of the participants' time.

#### Body composition

Weight is measured in light clothing without shoes to the nearest 0.2 kg using a digital balance (SECA 888) and height is measured to the nearest 0.1 cm with a stadiometer (SECA 225). BMI (kg/m^2^) will be used as an index of relative weight. Waist-circumference was measured at the level of the belly button and the hip-circumference at the level of the trochanter-major. Both circumferences were measured using a spring loaded measuring tape (SECA 200) to the nearest 0.1 cm. The four skinfolds (biceps, triceps, subscapular and supra-iliac) are measured twice with a Harpenden skinfold caliper (Baty International, England) and averaged, according to earlier research for adolescents [29] and young adults [30]. If the difference between these two measurements was more than 1 mm, the measurement is done a third time.

### Sample size

The aim of the study is to establish a difference between the intervention and the control group of 20% in the proportion of subjects who are active according to the Dutch guidelines. Significance between the groups can be established with 80% (1-β) probability and a significance level of 0.05 (α). To be able to detect a difference of 20% in PA level, two groups of 50 subjects for each age group are required. Since we expect a dropout rate of 33 %, approximately 150 adolescents and 150 employees will be invited for the intervention.

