### Introduction

The positive health benefits of physical activity in people of all ages have been extensively studied and are now commonly accepted. There is compelling evidence that regular physical activity increases physical functioning, aerobic fitness and quality of life and favourably influences many risk factors for chronic diseases, such as coronary heart disease, colon cancer and type 2 diabetes mellitus [1,2]. Nonetheless, people in industrialized countries continue to reduce their energy expenditure in daily living and at work. Leisure time activities have become more sedentary, with television watching, playing videogames, and personal computer usage among the most popular sedentary pastimes [3,4]. Especially during adolescence and young adulthood a steep decrease in physical activity is seen [5-7]. Adolescents are recommended to perform at least moderate physical activity with a minimum of one hour a day [8,9]. In 2004, only 31% of the male and 18% of the female adolescents (12–17 yrs) in the Netherlands complied with this guideline, according to data of the StatLine of the Dutch Central Bureau of Statistics [10]. Adults are advised to perform at least moderate physical activity for a minimum of 30 minutes on at least five days of the week. In 2004, only 50% of the Dutch young men and 55% of the women (25–35 yrs) were sufficiently active according to this guideline. An effective intervention to promote physical activity in these specific age-groups could therefore provide enormous health gains [11]. In a cross sectional study [12] among 2600 adults in the Netherlands was shown that 60% of the people that did not meet 30 minutes of physical activity on at least five days of the week, overestimated their own physical activity levels. Hence, feedback on the actual amount of physical activity per day may overcome this problem of poor self-evaluation and thereby positively affect the physical activity level among inactive persons.

One way to provide direct feedback on the actual amount of physical activity is via a physical activity monitor. Physical activity monitors can be worn without major inconvenience, requires little effort of the user and are compatible with most daily activities, making it a practical and socially acceptable measure of physical activity. Moreover, in a study of Rooney et al. [13], an increase in awareness of daily activity and increased physical activity was found, after wearing a pedometer for eight weeks.

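### The 80% power claimed in each age group needs a control rate of about 5–6% or less in a two-sided test; this is unstated and hard to reconcile with the protocol's young-adult figures

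*Protocol article*

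**What the plan says.** The Sample size section of the protocol article aims at "a difference between the intervention and the control group of 20% in the proportion of subjects who are active according to the Dutch guidelines". It adds that "Significance between the groups can be established with 80% (1-β) probability" at a significance level of 0.05, and states: "To be able to detect a difference of 20% in PA level, two groups of 50 subjects for each age group are required". It then allows for loss: "Since we expect a dropout rate of 33 %, approximately 150 adolescents and 150 employees will be invited for the intervention". No control-group proportion and no sidedness are given.

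Three other places bear on the control proportion:

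- **Introduction.** In 2004 "only 50% of the Dutch young men and 55% of the women" aged 25–35 met the adult guideline. For adolescents aged 12–17 the figures are 31% of males and 18% of females.
- **Study design and Selection for intervention.** The less active half of those screened is enrolled. The rule adds a PAM quartile to an AQUA quartile, takes sums below 5, and lets the AQUA quartile decide at 5.
- **Recruitment, Young adults.** Adults are office workers, chosen partly because their work is mostly sedentary.

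**The concern.** The number needed to detect a fixed 20-point difference depends strongly on where the control proportion lies. Over the range that matters for an inactive sample it roughly doubles, from 49 to 97 per group. The section makes a definite power claim for each age group separately, and the Statistical analysis section pre-plans analyses by age group. If power for the guideline proportion in adults is well below 80%, an inconclusive adult comparison on that outcome would be judged against a sensitivity the design probably does not have.

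**Working it through.** **Inputs from the protocol:** difference Δ = 0.20 (read as percentage points), power 80%, α = 0.05, 50 per group per age group, dropout 33%. **Assumed:** a two-sided test, since sidedness is not given, and a range of control rates p₁, with p₂ = p₁ + 0.20 and p̄ their mean.

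**Formulas (pooled-variance comparison of two proportions):**

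n per group = [1.960·√(2p̄(1−p̄)) + 0.842·√(p₁(1−p₁)+p₂(1−p₂))]² / Δ²

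power = Φ{[Δ√n − 1.960·√(2p̄(1−p̄))] / √(p₁(1−p₁)+p₂(1−p₂))}

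**Step 1: can 50 be reproduced?** Yes, at 5% vs 25%:

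- n = (1.960×0.505 + 0.842×0.485)² / 0.04 = 48.8, so 49.
- Power at 50 = Φ[(1.414 − 0.990)/0.485] = 81%.

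A one-sided test at 10% vs 30% also gives 49. The dropout step reproduces: 100/(1 − 0.33) = 149.3, about 150.

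**Step 2: other control rates, two-sided.**

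| Control rate | n per group for 80% | Power at 50 per group | Power at 100 per group |
|---|---|---|---|
| 5% | 49 | 81% | 98% |
| 6% | 52 | 79% | 98% |
| 10% | 62 | 71% | 95% |
| 20% | 82 | 59% | 88% |
| 30% | 93 | 53% | 83% |
| 40% | 97 | 52% | 81% |

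Power is lowest at 40% vs 60%. It recovers to 81% at 75% vs 95%, but so high a control rate is irrelevant to an inactive sample.

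**Step 3: a floor for adults that needs no correlation model.** Suppose screened adults resemble the national figure, at the midpoint (50 + 55)/2 = 52.5%. Then 47.5% do not meet the guideline, but 50% are selected. Even with perfect sorting, (50 − 47.5)/50 = 5% of those selected meet it. At 50% adherence the floor is 0%; at 55% it is (50 − 45)/50 = 10%. At the midpoint, 80% power therefore needs essentially flawless sorting and no later drift.

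**Step 4: sorting cannot be flawless.** The rule ranks on quartiles, not on the guideline. PAM quartile 1 with AQUA quartile 3 sums to 4, so some people above the AQUA median are enrolled. The outcome is a later 7-day recall, so regression to the mean is expected. To size this I simulated the rule, taking a sum of 5 as inactive when the AQUA quartile is 1 or 2; this selects 50%, as the Study design section intends. The following are assumptions, not figures from the protocol: bivariate normal scores, PAM–AQUA correlation 0.3, correlation of AQUA between selection and follow-up (stability) of 0.4–1.0, guideline status as a cut on the AQUA scale, and no stratification by education.

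Adults, 52.5% adherent before selection:

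| AQUA stability | Control rate | Power at 50 per group |
|---|---|---|
| 0.4 | 41% | 52% |
| 0.6 | 34% | 52% |
| 0.8 | 26% | 55% |
| 0.9 | 22% | 58% |
| 1.0 | 14% | 65% |

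Starting from 50% or 55% instead of the midpoint widens the ranges to about 10–43% for the control rate and 52–70% for power.

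**Step 5: less active office workers.** If only 35–40% of screened adults meet the guideline (an assumption), power runs from about 54% (40%, stability 0.4) to 84% (35%, stability 1.0).

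**Step 6: adolescents.** At (31 + 18)/2 = 24.5%, power is about 64% at stability 0.4, 80% at 0.8, and higher above that.

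**The case against.** A reader might infer that the 50 per group is an arithmetic error. It is not: 5% vs 25% two-sided, or 10% vs 30% one-sided, returns 49. The figure cannot be verified as written, but it is not impossible.

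A reader might also infer that the protocol's own adherence figures imply near coin-flip power in adults. They do not. Those are national background figures and are not offered as sample-size inputs. The trial enrols the less active half of sedentary office workers, and the model's correlations are not in the document. With a lower starting adherence and near-perfect stability, adult power can reach the claimed 80%. In adolescents the claim is defensible on plausible inputs.

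Two further limits stand. The primary analysis is of change in physical activity, which the protocol expresses in minutes per week and a total score, so the power of a dichotomised comparison does not show that analysis to be underpowered. And an article may leave the control proportion and sidedness to the full protocol, so omission alone would not be a finding.

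What the objection does not remove is that the section makes a definite claim for each age group. In adults that claim holds only at a control rate which the Introduction and the selection rule make hard to credit.

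**Conclusion.** The concern holds in a limited form. With a two-sided 5% test, 80% power at 50 per group requires a control rate of about 5–6% or lower; at 10% power is 71%, and at 20–40% it is 59–52%. For young adults the stated power is probably not delivered on the guideline outcome: about 52–65% if screened adults resemble the national midpoint, and about 54–84% if 35–40% of them meet the guideline. Both ranges rest on the model assumptions listed above and are illustrations, not estimates from the protocol. For adolescents, about 64% to above 80% is supportable, so 80% is attainable but not assured. Nothing here shows that the change-in-activity analysis lacks power.

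**What to change.** In the Sample size section:

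- State the assumed control proportion meeting the guideline in each age group after selection, with its justification, and whether the test is one- or two-sided.
- Replace the blanket 80% per age group with the power at 50 per group over a plausible range of control rates, for example 81/71/59/53/52% at 5/10/20/30/40% (two-sided).
- Add that the two age groups combined, 100 per arm, give at least 81% at any control rate. This requires a 20-point difference in both age groups, each judged against its own guideline, and makes no allowance for clustering. The margin is small: 97 per arm are needed at 40% vs 60%.
- Make clear that these figures concern the dichotomised guideline outcome, not the change-in-activity comparison in the Statistical analysis section.

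The cost is rewording and a less favourable stated power for adults. No extra recruitment is needed.

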### Statistical analysis

The primary analysis will be a comparison of the change in physical activity (PA) between the intervention and control group following the "intention to treat" principle. To adjust for the dependency between observations of subjects from the same school and class or company, multilevel analysis will be performed. Intention to treat analyses will also be performed for the secondary outcomes; determinants of physical activity, quality of life, empowerment, aerobic fitness and body composition. Pre-planned subgroup analyses will be performed for adolescents and adults and separate for gender. Where appropriate, adjustments will be made for differences at baseline values. Per protocol analyses will also be carried out.

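### The aim and the 80% power are stated for the proportion meeting the activity guidelines, but the primary outcome and analysis are the change in questionnaire-measured activity, so the aim has no planned test and the power belongs to a different one

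*Protocol article*

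**What the plan says.** All references are to the protocol article.

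- **Sample size.** The aim is to show "a difference between the intervention and the control group of 20% in the proportion of subjects who are active according to the Dutch guidelines", with 80% power at a significance level of 0.05. The next sentence describes the target differently: "To be able to detect a difference of 20% in PA level, two groups of 50 subjects for each age group are required". Dropout is then added: "Since we expect a dropout rate of 33 %, approximately 150 adolescents and 150 employees will be invited for the intervention".
- **Measurements.** "The primary outcome of the intervention study is the level of physical activity measured by questionnaire". The secondary outcomes are determinants of activity, quality of life, empowerment, aerobic fitness and body composition. Meeting the guideline is in neither list. The questionnaire is given at baseline, after the 3-month intervention and again five months later.
- **Questionnaire, Physical activity.** "Physical activity will be expressed in minutes per week and in a total activity score", the score being minutes multiplied by MET value. Light activity is recorded, starting at 2 MET. No category for meeting the guideline is defined.
- **Statistical analysis.** "The primary analysis will be a comparison of the change in physical activity (PA) between the intervention and control group", by intention to treat and multilevel analysis, with baseline adjustment where appropriate.
- **Introduction.** The guidelines count activity of at least moderate intensity: an hour a day for adolescents, and half an hour on five or more days a week for adults.

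**The concern.** The quantity that justifies the sample size should be the quantity that the primary analysis tests. Here the first is a yes/no status and the second, as the Questionnaire section scores it, is a continuous amount.

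The two can give different answers. Under the AQUA bands, a minute of light activity adds 2 to 5 units to an adolescent's total score (2 to 4 for an adult) and nothing towards the guideline. The score can therefore rise with nobody newly meeting the guideline. Conversely, a modest shift among people just under the threshold can change the proportion while barely moving the mean.

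Two things are at stake. A reader could not tell from the primary result whether the stated aim was met. And the quoted 80% says nothing definite about the test that decides the trial.

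**Working it through.** **1. The plan's own figure.** Inputs from Sample size: difference 0.20 (read as percentage points), power 80%, alpha 0.05 (taken as two-sided; the article does not say), 50 per arm, dropout 33%. The control proportion p1 is not given, so 50 cannot be reproduced from the article alone. With the pooled two-proportion formula

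n = [1.96·√(2·p̄·(1−p̄)) + 0.8416·√(p1(1−p1) + p2(1−p2))]² / 0.20²

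- 5% v 25%: p̄ = 0.15, so n = (1.96·√0.255 + 0.8416·√0.235)² / 0.04 = 1.954 / 0.04 = 48.8, i.e. 49.
- 6% v 26%: n = 52.

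So 50 per arm is consistent with a control rate of about 5 to 6%. Dropout: 100 / (1 − 0.33) = 149.3, which agrees with about 150.

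This confirms that the figure can be a two-proportion calculation. It does not show that 50 is wrong.

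**2. What 50 per arm gives for a continuous endpoint.** With two means, equal arms and no clustering, the detectable difference in SD units is

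(1.96 + 0.8416)·√(2/50) = 2.8016 × 0.2 = 0.56 SD.

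Here SD means that of the quantity analysed. The article gives neither that SD nor a target mean difference, so 0.56 SD cannot be turned into minutes or MET-minutes. An allowance for clustering would raise it. Baseline adjustment would lower it: with an assumed baseline correlation of 0.6, 0.56·√(1 − 0.36) = 0.45 SD of the follow-up measure.

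**3. Direction of the power error.** Power at 50 per arm for a true standardised difference d is Φ(5d − 1.96): 32% at d = 0.3, 71% at 0.5 and 85% at 0.6. To link d to the guideline proportions, assume purely for illustration a normal scale that is cut at the guideline, so that d = z(p2) − z(p1):

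| Assumed control v intervention | Power, two proportions | Implied d | Power, continuous |
|---|---|---|---|
| 5% v 25% | 81% | 0.97 | 99.8% |
| 10% v 30% | 71% | 0.76 | 97% |
| 20% v 40% | 59% | 0.59 | 84% |
| 40% v 60% | 52% | 0.51 | 72% |

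Under this assumption the continuous test has more power than the binary one in every row, yet it lies on either side of the stated 80% depending on the unstated control rate. If the real effect on the AQUA measure is smaller than this scale implies, for instance d = 0.3, power is far below 80%. The article contains nothing that selects among these cases.

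**The case against.** The best defence is that the Statistical analysis section never says continuous. It says change in physical activity, and a multilevel model can be logistic. Sample size itself moves from the guideline proportion to PA level, and Measurements calls the primary outcome the level of physical activity, so guideline status derived from the AQUA might be meant as one expression of that level.

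Part of this stands: the continuous scale is inferred from Measurements and Questionnaire together. But Questionnaire lists only minutes and a score, and no outcome or analysis section names guideline status. The article would have to say that adherence is the primary variable, and it does not. Nor is this detail left to an analysis plan, since the article itself states both the aim and the primary analysis, and they differ.

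Three stronger readings are tempting and are not supported:

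- **That the trial is underpowered.** The mismatch does not show this. As the table shows, the power of the continuous test may be above or below 80%.
- **That several primary tests will be run and the false-positive rate is inflated.** Two expressions and two follow-up times are described as scoring and schedule. No section plans a separate primary test for each, and that choice is commonly left to a fuller document.
- **That 20% in PA level means 20% of mean activity, which would need far larger numbers.** The preceding sentence defines the 20% as a difference in proportions, and no coefficient of variation is given.

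**Conclusion.** The point holds as an internal contradiction. The aim and the 80% power (50 per arm per age group) refer to the proportion meeting the guidelines, while the primary outcome and analysis refer to change in questionnaire-measured activity. Following the article as written leaves the stated aim untested and attaches the power statement to a test that is not primary.

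The error in power has no determinable size or sign. What can be said is that 50 per arm corresponds to 0.56 SD on a continuous endpoint, assuming a two-sided 5% test, equal arms, no clustering allowance and no baseline adjustment. The article neither states nor justifies that difference. The conclusion also rests on reading the primary outcome as continuous, which is the natural reading of the Questionnaire section.

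It should be put right because the repair is cheap and, by the article's own account, no results were known when it was written.

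**What to change.** Align Sample size, Measurements and Statistical analysis in one of two ways.

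- **(a) Follow the stated aim.** Make guideline adherence derived from the AQUA the primary outcome, with the derivation rule written down for each age group, and analyse it by multilevel logistic regression. State the control proportion behind the 50 per arm; at two-sided 5% without continuity correction, 50 fits about 5 to 6%. Keep change in activity as secondary.
- **(b) Follow the stated analysis.** Keep change in activity as primary and name one expression and one time point, for example minutes per week of at least moderate activity at 3 months, since that is the intensity the guidelines use. List guideline adherence as secondary. Replace the power sentence with a detectable difference for that endpoint: 0.56 SD at 50 per arm before any clustering allowance, larger with one, smaller with baseline adjustment. Give the SD that turns it into minutes.

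Under either option, replace the phrase about a 20% difference in PA level with the quantity actually meant. The cost is wording and a recalculated power statement. Aligning the sections needs no new measurement and no extra enrolment.
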